**Secondary hypotheses**
Change in positive emotions among participants using the Dispositional Positive Emotions Scale [54]Change in mental health self-stigma among participants using the Self-Stigma of Mental Illness Scale-Short Form [53]Change in public mental health stigma among participants using the Difference and Disdain Scales for Public Stigma [55]

## Methods

### Overview

This is a multiphase, mixed methods project that uses both qualitative and quantitative methodologies (Figure 1). Qualitative findings will be used to deepen the understanding of the quantitative results by (1) exploring differences between video testimonies and digital stories using discourse analysis and (2) conducting a thematic analysis of in-depth individual interviews. Phase 1 (months 1-9) will involve a preparatory search to identify Canadian social marketing and fundraising campaigns. Digital storytelling workshops (phase 2) will be held simultaneously, and in-depth interviews conducted before and after each workshop. In phase 3 (months 10-21), a pilot RCT will be undertaken, involving additional in-depth interviews. In phase 4 (months 22-24), knowledge mobilization will be conducted.

**Figure 1 figure1:**
[figure not shown]
Learning to care project logic model.

### The Study Process and Outline

#### Phase 1: Identification of Social Marketing and Fundraising Campaigns

##### Knowledge Synthesis Activities Identifying Social Marketing and Fundraising Campaigns (Completed)

Canadian public and social marketing campaigns that include video testimonies on mental illness, mental or emotional distress, and recovery were identified using a web-based search engine (Google). The websites of organizations dedicated to improving mental health and well-being (eg, the Canadian Mental Health Association, Canadian mental health hospitals, and their associated foundations) were identified and searched for campaign materials. All video testimonies identified from these campaigns and organizational websites were collected and will be analyzed. The search was supplemented by a Google video search to locate other publicly disseminated video testimonies. The searches were conducted from April to September 2021 to capture the most visible Canadian campaigns at the start of the study. Videos selected from each identified campaign included all the available first-person video testimonies, 1 to 5 minutes in duration, as well as television commercials and video advertisements in English and French. Campaign materials created as fact sheets involving substantial written text or image-based materials (eg, billboards, webpage advertisements, magazine advertisements, and slogans) were excluded. This study aims to gather 10 to 30 video testimonies for evaluation (phase 3).

##### Recruitment

Social and community mental health services in Montreal and local universities will be contacted to promote, and host, 3-day digital storytelling workshops designed to produce a wide range of stories about recovery from mental illness that elicit emotions such as hope and compassion. Invitations to participate in the workshops will be posted (6 workshops: 8-10 participants each, generating up to 60 digital stories). Maximum variation sampling [63,64] will be used to determine participant composition in the workshops. Maximum variation sampling captures a wide range of perspectives by involving participants who represent a wide variety of identities, including gender, language, and sociocultural background, as well as different experiences of mental illness. Participants will be invited to an individual preworkshop meeting with the principal investigator where the subject matter for the stories (mental illness and recovery journey) and workshop structure will be explained.

Workshop participants (*storytellers*) will be invited to reflect on and depict moments involving emotions such as fear, shame, doubt, hope, courage, empathy, and warmth. Short digital videos created during each workshop will also be used for the evaluation of the study. The stories produced will remain the property of participants, who will each receive a media release form at the end of their workshop specifying if, how, and when their digital stories may be used. For this reason, we are soliciting the creation of approximately 60 digital stories for later use in the RCT. Workshop participants will be invited to a short interview before the workshop, and a longer interview soon afterward, to explore their experiences and story-sharing processes.

In-person workshops will be implemented based on participant availability and preferences. However, the workshops may also be implemented remotely for the duration of the COVID-19 pandemic to ensure participant safety. Specifically, participants will be offered a remote access option for involvement in the study (eg, preworkshop meeting with the principal investigator, screening, interviews, and data collection) using a secure, approved platform (Microsoft Teams). In addition, the web-based workshops will not operate under the full 3-day format, as originally planned, but will be split into short internet-based meetings, 3 hours each, and conducted over a 5-day period.

This project embraces *ethical practices in digital storytelling* [65]. The principal investigator and project coordinator will explain the consent form to participants at the preworkshop meeting, informing them of their rights, the purpose of the study, workshop structure and content, potential risks and benefits of sharing digital stories on the web, data collection processes and methods, and procedures for maintaining data confidentiality. Participants will have the opportunity to ask questions before signing the consent form. Written informed consent will be obtained from all the participants.

All workshop participants will participate in brief pre- and postworkshop interviews (n=60). Data will be analyzed thematically using a data-driven (inductive) approach rather than a theory-driven (deductive) approach. In this phase, the thematic analysis offers a useful method for examining the similarities and differences in the views of the research participants, generating rich insights. On the basis of a well-structured approach to handling data, thematic analysis is useful for producing clear, well-defined themes, subthemes, and relationships between them [55,66]. Following this approach, codes will reflect the discovered themes and meanings [67]. Braun and Clarke [66] guidelines for thematic analysis will be followed: (1) generating initial codes and searching for themes (collating codes into potential themes) and (2) reviewing and redefining themes.

#### Phase 3: Pilot RCT

##### Participants

A parallel 2-arm RCT design will be used to assess the impact of digital stories made by ordinary people compared with digital narratives used in social marketing and fundraising campaigns. A convenience sample of university students (n=80; age 18-35 years) from McGill University will be invited to participate in the pilot RCT, as a population comfortable with accessing web-based visual content and relatively easy to engage within the project timeline.

##### Sampling

The project coordinator will assess participant eligibility, obtain consent, and facilitate data collection (eg, log-in to the REDCap platform). Participants will choose an option for the screening and consent processes, whether in person, by phone, or video call using a secure platform (Microsoft Teams). Before seeking consent, the project coordinator will explain the consent form to RCT participants, informing them of the study objective, potential risks and benefits of participation, expected study duration, data collection processes, and methods and procedures for maintaining data confidentiality. Participants will be invited to ask questions before signing the consent form. Written informed consent will be obtained from all participants.

##### Randomization Procedure

Participants will be randomly assigned (1:1 ratio) to the social marketing or fundraising group (20/40, 50% Anglophone and 20/40, 50% Francophone participants) or the digital storytelling group (20/40, 50% Anglophone and 20/40, 50% Francophone participants) using the SAS, Stata, or R software. One of the arms of the pilot RCT will expose the participants to digital storytelling videos (intervention group), whereas the second arm will expose the participants to social marketing and fundraising videos (active control group). For both arms, sensitive content will be discussed with participants before screening of the videos so that certain content may be skipped over as needed.

The inclusion criteria for the study are as follows:

Individuals of 18-35 years of ageIndividuals not currently treated in a hospital inpatient

The exclusion criteria for the study are as follows:

Individuals outside the age range (18-35 years)Individuals currently treated in a hospital inpatientIndividuals who attended a digital storytelling workshop and made a digital story used in the RCT

##### Methods of Assessment and Measurement

Participants will complete the first set of measures (time 1) before exposure to either study condition. Digital narratives will be assessed using a between-subjects design, in which each participant will view only video testimonies (social marketing or fundraising group) or only the digital storytelling videos (digital storytelling group). The system will record this information. Participants in each group will be exposed to a maximum of 10 video testimonies or digital stories. They will also complete standardized scales and a series of multiple-choice and open-ended questions regarding their perceptions of each digital video testimony or digital story. The duration of the survey will be 15 to 20 minutes.

Using a secure platform, a web-based survey comprising a variety of standardized scales, multiple-choice questions, and open-ended questions will be developed to assess video testimonies from social marketing or fundraising campaigns versus digital stories for their impact on empathy and compassion. The following scales will be used: Level of Familiarity scale (11-item questionnaire), which assesses the degree of contact with people living with specific diagnoses and will be used only before exposure to movies [68]; Toronto Empathy Questionnaire (16 items; Cronbach α=.79; test–retest reliability coefficient 0.73) [52]; Compassionate Love Scale (21 items; Cronbach α=.95; item-to-total correlations 0.46-0.81) [53]; Dispositional Positive Emotions Scale (5 items; Cronbach α=.80 [compassion subscale]; interscale correlation 0.44) [54]; Self-Stigma of Mental Illness Scale-Short Form (20 items; Cronbach α=.91) [69]; and Difference and Disdain Scales for Public Stigma (9 items) [70]. Examples of multiple-choice and open-ended questions are as follows:

Why do you think this video was made? (response options: promote awareness, promote knowledge about services, promote knowledge about the organization, raise money, etc)How much control did the person in the video have over the story?How much control did the person in the video have over production of the video (eg, images music, etc)?How much control did the person in the video have over editing?How much control did the person in the video have over its dissemination or use?How much did watching these videos affect you?What was the most important thing you learned?

##### Data Management and Analysis

Mean group differences in scores on the selected measures from baseline to postintervention will be analyzed using repeated-measures analysis of variance, with intervention as the between-subjects factor and time the within-subjects factor, and with an interaction term (time and interaction group). To address feasibility questions, we will use descriptive statistics from standard operating procedures (eg, screening tools or data) and data collected (eg, number of participants, recruitment rates, and refusal rates).

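### The planned repeated-measures ANOVA is valid but amounts to a change-score t-test; ANCOVA on the baseline scores already collected would be modestly more precise

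*Protocol article*

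**What the plan says.** The Data Management and Analysis section analyses "Mean group differences in scores on the selected measures from baseline to postintervention" by "repeated-measures analysis of variance, with intervention as the between-subjects factor and time the within-subjects factor", "with an interaction term (time and interaction group"), which evidently means time by intervention group. The article describes two measurement occasions. For the first, "Participants will complete the first set of measures (time 1) before exposure to either study condition"; the second follows exposure, and no later follow-up is mentioned.

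The design is a two-arm comparison in "A convenience sample of university students (n=80; age 18-35 years) from McGill University", with 1:1 random allocation, hence 40 per arm. The Randomization Procedure section also gives 20 Anglophone and 20 Francophone participants in each arm. The two primary hypotheses concern empathy (Toronto Empathy Questionnaire) and compassion (Compassionate Love Scale). The stated model does not adjust for baseline.

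**The concern.** With only two occasions, a repeated-measures ANOVA does no more than subtract baseline from postintervention and compare the arms. Subtraction fixes the coefficient on the baseline score at 1. In a randomised comparison with equal SDs at the two times, the best coefficient is the baseline-to-post correlation, which is below 1 for any imperfectly stable scale. The plan therefore collects baseline scores on every outcome and then uses them less efficiently than it could.

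What is at stake is the width of the interval around each arm difference. This matters even though feasibility is the pilot's main purpose, because the scientific-basis questions in the Quantitative Research Methodology section ask for the estimated intervention effect and its variance. The model choice bears directly on both.

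**Working it through.** The article gives no alpha, power, effect size or SD, so there is no sample-size figure to reproduce.

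**Inputs**
- Two occasions and two arms: Data Management and Analysis; Methods of Assessment and Measurement.
- n = 40 per arm: 80 participants allocated 1:1 (Participants; Randomization Procedure).
- r, the baseline-to-post correlation: not stated. The nearest figure is in "Toronto Empathy Questionnaire (16 items; Cronbach α=.79; test–retest reliability coefficient 0.73"). I use 0.73 as a proxy and show a range.
- Assumptions: equal SD σ at both times (σ = 1 below), complete pairs, two-sided alpha 0.05.

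**Step 1: equivalence.** Let D be postintervention minus baseline. With two occasions, the within-subject part of the ANOVA depends on the data only through D. The time-by-group term compares mean D between arms, and its error term is the pooled within-arm variation of D on 78 degrees of freedom. Hence F(1,78) = t². On one simulated data set of 40 per arm, F from the sums of squares and the squared change-score t were both 3.4154, each with p = 0.0684.

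**Step 2: variances per participant.**
- Change score: 2(1−r) = 2 × 0.27 = 0.540.
- ANCOVA: 1−r² = 1 − 0.5329 = 0.467.
- Ratio: (1−r²)/[2(1−r)] = (1+r)/2 = 0.865.

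**Step 3: cost of estimating the slope.** The ANCOVA variance is inflated by about 1 + 1/(2n−4) = 1 + 1/76 = 1.013, so the ratio becomes 0.865 × 1.013 = 0.876. Simulating 10,000 trials gave 0.873.

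**Step 4: standard error of the arm difference.**
- Planned test: √(0.540 × 2/40) = 0.164 SD.
- ANCOVA: √(0.467 × 1.013 × 2/40) = 0.154 SD.
- 95% half-widths: 1.991 × 0.1643 = 0.327 SD and 1.991 × 0.1538 = 0.306 SD.
- Equivalent sample size: 80/0.876 ≈ 91.

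**Step 5: range of r.**

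| r | Ratio (1+r)/2 | Gain before slope cost | Ratio after slope cost | SE, planned (SD) | SE, ANCOVA after slope cost (SD) |
|---|---|---|---|---|---|
| 0.5 | 0.750 | 25% | 0.760 | 0.224 | 0.195 |
| 0.73 | 0.865 | 13.5% | 0.876 | 0.164 | 0.154 |
| 0.8 | 0.900 | 10% | 0.912 | 0.141 | 0.135 |
| 0.9 | 0.950 | 5% | 0.962 | 0.100 | 0.098 |
| 0.95 | 0.975 | 2.5% | 0.988 | 0.0707 | 0.0703 |

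The slope cost cancels the gain when (1+r)/2 × 1.013 = 1, that is, at r of about 0.97.

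**Step 6: illustrative power.** For an assumed true difference of 0.4 SD and r = 0.73, t-based power is 0.67 for the planned test and 0.73 for ANCOVA. The plan sets no power target, so these figures only show scale.

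**The case against.** The strongest reply is that nothing here is wrong. The interaction test is a standard method, valid under randomisation, in a pilot that puts feasibility first and claims no power. At r = 0.73 the 95% half-width narrows by about 0.02 SD, which would hardly change a pilot's conclusions. The proxy is also weak: the article gives neither the retest interval behind 0.73 nor the pre-to-post interval in this trial, and it has no comparable figure for the Compassionate Love Scale. If these largely dispositional scales correlate at 0.9 or more over a short interval, the gain nearly vanishes. All of this stands, and it limits the point to efficiency.

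It does not remove the point. The model is stated in the text rather than left to a fuller document, the pilot intends to report the effect and its variance, and the better analysis uses scores already in hand.

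A reader might infer more than the article supports:
- *That chance baseline imbalance is a further harm.* It is the same loss counted again: 0.540 − 0.467 = 0.073 = (1−0.73)², which is the imbalance variance carried through the change score.
- *That the group or time main effect will be taken as the treatment effect.* The section targets group differences from baseline to postintervention and includes an interaction. It nowhere says a main effect will be read that way.
- *That leaving out the Level of Familiarity scale is a flaw.* The article says it measures contact with people with specific diagnoses and "will be used only before exposure to movies". It does not present the scale as a predictor of the outcomes, and a condensed article may leave covariate lists to the full protocol.

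**Conclusion.** The point holds as one of efficiency. The planned group-by-time test is a change-score t-test: unbiased, with correct alpha, and less precise than baseline-adjusted ANCOVA unless r exceeds about 0.97 at this sample size. It would be wrong to conclude that the planned analysis is invalid.

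For the Toronto Empathy Questionnaire, with 0.73 as a proxy, the net variance reduction is about 12% and the standard error is about 6% smaller. For the Compassionate Love Scale the direction is the same but the size is unknown, because the article gives no value for r. The figures assume equal SDs at both times, complete pairs and 40 per arm.

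**What to change.** In Data Management and Analysis, replace the repeated-measures ANOVA for each scale with an ANCOVA of the postintervention score on arm and the baseline score of the same scale. Add language as a covariate if allocation is balanced by it, as the 20/20 split per arm suggests. Report the adjusted arm difference with its 95% CI. A longitudinal model with a common baseline mean for the two arms is an acceptable equivalent.

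The observed baseline-to-post correlation could usefully be reported for each scale, since a later trial would need it for its sample size. The cost is a change of analysis wording; no new data, participants or procedures are needed.

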#### Phase 4: Knowledge Dissemination

The knowledge dissemination plan will use targeted strategies and tools to make findings readily accessible. Identified knowledge users include academics from multiple disciplines, government policy makers, organizational decision-makers, and the public. Findings will reach the academic community through presentations at international conferences and publications in peer-reviewed journals. Web platforms will be used to reach government policy makers, nonprofit or for-profit organizations, and other stakeholders, favoring content in the form of brief reports (French and English) and infographics. With participant consent, digital stories will be submitted for release at future public events, including short film festivals, to promote ongoing public dialog.

### Trustworthiness, Validity, and Reliability

This study uses Lincoln and Guba [71] concept of trustworthiness, which is based on the following criteria: credibility, transferability, dependability, and confirmability. Credibility will be achieved using data collection triangulation and analysis. *Distinctive data collection activities will be implemented and a systematic search performed* to identify social marketing and fundraising campaigns (video testimonies) and analyzed using visual discourse analysis. Digital storyteller workshops will be implemented to generate digital stories that will be analyzed using visual discourse analysis. Interviews will be conducted with workshop participants to further investigate their experiences, and interviews will be analyzed using thematic analysis. At the end of each activity (data synthesis, implementation of workshops and interviews, and data analysis), the research team will hold a debriefing session on the research process, which will also increase credibility. Transferability, which refers to the generalizability of the qualitative inquiry and findings, will be operationalized through a detailed description of the methodological steps taken and an explanation of the process by which the definitive findings were generated and interpreted. To achieve dependability, the research team will document each phase so that the activities and decisions taken are transparent [71,72]. A logic model (Figure 1) describing the research process has been created to demonstrate dependability in the event of a study audit. According to Guba and Lincoln [73], confirmability, concerned with the grounding of interpretations and findings in the data, is established when credibility, transferability, and dependability are all achieved. As mentioned, the research team will rigorously disclose the reasons for the methodological and analytical choices made throughout the study [72].

To promote the validity and reliability of the RCT, this project has been registered, and CONSORT (Consolidated Standards of Reporting Trials) will be used to report the methodology and outcomes of the pilot trial.

## Results

The study was approved by the research ethics board of the Douglas Hospital Research Centre, Montreal, Canada, in March 2021. The study design adheres to the CONSORT guidelines for reporting pilot RCTs [74,75]. Anticipated time to completion within the 2-year study period includes 9 months for phases 1 (knowledge synthesis activities identifying social marketing and fundraising campaigns) and 2 (digital storytelling workshops), 11 months for phase 3 (feasibility assessment and data collection: RCT), and 2 months for phase 4 (knowledge dissemination).

The short- and long-term objectives of the project are to (1) analyze how mental and emotional distress is depicted in social marketing or fundraising campaigns versus digital stories created by *ordinary* people, (2) implement a digital storytelling workshop in the community and create a collection of digital stories that capture emotional encounters involving compassion (eg, fear, shame, doubt, hope, courage, warmth, and genuineness), (3) assess the impact of social marketing or fundraising campaigns and digital stories created by *ordinary* people for viewer empathy and compassion, (4) explore the subjective experience of creating a personal story about mental and emotional distress in relation to theoretical formulations of empathy and compassion, and (5) explore the subjective experience of viewing digital stories about mental and emotional distress and compare this experience with the theoretical formulation of empathy and compassion.

